#### Participants

The population consists of LBP patients (18–65 years) who visit an outpatient clinic (mainly orthopaedics and neurology, but also rheumatology and neurosurgery) of one of the participating hospitals. The population has to 1. have LBP lasting more than 12 weeks, 2. have paid work (i.e. paid-employment or self-employed) for at least 8 hours a week and 3. be on (partially) sick leave. Patients will be excluded from the study in case of 1) being sick listed more than two years; 2) working temporarily for an employment agency without detachment; 3) having specific low back pain, due to infection, tumor, osteoporosis, rheumatoid arthritis, fracture or inflammatory process; 4) having had a lumbar spine surgery in the last 6 weeks or having to undergo surgery or invasive examinations in the near future (within 3 months); 5) having serious psychiatric disorders; 6) having cardiovascular or medical contraindications for physical activity according to the Physical Activities Readiness Questionnaire (PAR-Q) [16]; 7) being pregnant or having given birth in the last 3 months; 8) dealing with a lawsuit to their employer; 9) not having the ability to complete questionnaires written in the Dutch language.

In order to recruit a sufficient number of eligible patients, in each hospital a competent hospital employee will identify the source population weekly from the computerized patient record system. Within one week after the visit, the patients will receive three documents by mail: 1. a letter from their medical specialist in which they are informed about the study and asked if they are willing to participate, 2. a brochure with details of the study and 3. a short screening questionnaire. A return envelope is enclosed for returning the screening questionnaire to the researcher. On this questionnaire they can indicate if they are willing to participate in the study.

All patients who return the questionnaire, meet the criteria and indicate that they are willing to participate will be contacted by telephone. The researcher or a research assistant will provide additional information about the implications of participation and will check the eligibility of the patient. If a patient meets the selection criteria and is willing to participate, they will be asked to sign the informed consent.

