### Outcome measures

#### Primary outcome

The primary outcome is RTW defined as: "duration of sick leave in calendar days from the day of randomization until full RTW in own or other work with equal earnings, for at least 4 weeks without (partial or full) recurrence. In addition, the total duration of sick leave due to LBP (including all recurrences of sick leave episodes due to LBP) will be calculated for the entire follow-up period. Patients are asked monthly 1. to register the percentage of sick leave i.e. dividing the number of hours a patient is sick listed by the number of hours of the patients working week multiplying with a 100%; 2. the reason for being on sick leave, i.e. LBP, influenza ect. After a patient has been followed for a period of 12 months, a letter will be sent to the patient's occupational physician with the request to provide the sick leave data of the last 12 months registered in the data records of the occupational health services. Because some patients are self-employed, the self-reported data will be used for statistics.

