### Sample size

We assume that a Hazard Ratio (HR) of 2.0 indicates a relevant difference between the multidisciplinary outpatient care group and the UC group. This HR is based on HRs found in comparable studies in primary care [15,19,34]. Another assumption is that 40 percent of the sick listed patients due to chronic low back pain does not return to work during the follow-up period (12 months after randomization). We expect a dropout rate of 10%, based on experiences with comparable research [35,36]. To get a complete data set of 115 patients, 130 patients with chronic LBP who are sick listed will be included (HR = 2, with a power (1-β) of 80% and a significance level of 5%) [37]. Before starting the inclusion of patients, a two-week visitors' waiting room survey has been done at the departments of orthopaedics and neurology at the VU Medical Center Amsterdam. This survey showed that at these two departments the percentage of patients sick listed because of LBP is low (3–4%). Because of this low percentage, four other hospitals are recruited so the recruitment period of 24 months duration is likely acceptable.

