### Data analysis

All analyses will be performed at patient level. To examine the success of randomization, descriptive statistics will be used to compare the baseline measurements of the two groups. If necessary, analyses will be adjusted for prognostic dissimilarities. The primary independent variable in the analyses will be the treatment (MOC or UC) to which the patient is allocated. The primary dependent variable is sick leave duration in days until full return to own or equal work. Kaplan Meier analyses (including log rank test) will be used to describe the univariate association between group allocation and the sick leave duration until full RTW. The Cox Proportional hazard model will be used to analyze the HR of the RTW rates in both groups in a multivariate model. Longitudinal random coefficient analyses will be used to assess differences between treatment groups in improvement in all secondary outcome measures. The baseline value of the particular outcome variable will be added to the model in order to correct for possible regression to the mean.

All statistical analyses will be performed according to the intention-to-treat principle, i.e. the patients will remain in the group to which they were randomly allocated at baseline. In order to assess whether protocol deviations have caused bias, the results of the intention-to-treat analyses will be compared to per-protocol analyses. Only those patients who complied fully with the intervention protocol will be included.

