### Economic evaluation

Cost-effectiveness will be evaluated from the societal perspective including both direct and indirect costs. Both costs groups will be estimated according to the Dutch guidelines for cost analysis in health care research [38,39] or with the use of the tariffs of the Dutch Central Organization for Health Care Charges [40]. These costs will be measured 4 times during the one-year follow-up. Indirect costs of loss of production due to LBP are not related to health care, but are costs in paid and unpaid labour as a consequence of sickness, sick leave, disability and/or death of a productive person. Mailing the patient monthly a calendar as well as collecting the sick leave data collected in occupational health services database will measure the number of days on sick leave due to LBP. Quality of life will be measured according to the standard Dutch version of the EuroQol [30]. Costs will be summated for each individual patient. Bootstrapping will be used for pair-wise comparison of the mean groups to calculate mean differences in direct, indirect and total costs between the two groups of patients. Confidence intervals (95%) will be obtained by bias corrected and accelerated bootstrapping. A cost-effectiveness ratio will be calculated by dividing the difference between the mean costs of the intervention groups by the difference in RTW between the intervention groups. A cost-utility analysis will also be conducted in which the incremental costs per QALY will be estimated. Reliability of the cost-effectiveness ratios will be graphically presented on a cost-effectiveness plane and acceptability curves.

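### Degree of sick leave at entry (full or partial) is neither stratified nor a committed covariate; the primary analysis adjusts only if baseline differences seem to require it, and mean costs are compared unadjusted

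*Protocol article*

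**What the plan says.** - **Who enters.** Under Participants, a patient must "be on (partially) sick leave", so full and partial sick leave both qualify.
- **What counts as an event.** Under Primary outcome, the clock runs from randomization to full RTW sustained for four weeks. A partial return is not an event. Patients are asked each month "to register the percentage of sick leave i.e. dividing the number of hours a patient is sick listed by the number of hours" in their working week.
- **Stratification.** Under Randomization, the two factors are prior sick-leave duration (cut at 3 months) and mainly physical or mental work. Neither measures how much of the working week is lost.
- **Primary analysis.** Under Data analysis: "The Cox Proportional hazard model will be used to analyze the HR of the RTW rates in both groups in a multivariate model". No covariate is named. The same section compares the groups at baseline and allows adjustment for prognostic differences where that is judged necessary.
- **Secondary outcomes.** Directly after the random coefficient models for these outcomes: "The baseline value of the particular outcome variable will be added to the model in order to correct for possible regression to the mean". There is no counterpart for the primary outcome.
- **Costs.** Under Economic evaluation: "Bootstrapping will be used for pair-wise comparison of the mean groups to calculate mean differences in direct, indirect and total costs". No adjustment is described.
- **Baseline data.** Table 3 ticks Return to work at T0, without saying what that item records.

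**The concern.** At day 0 a partially sick-listed patient already works some of the contracted hours; a fully sick-listed patient works none. Both must reach the same endpoint, so degree of sick leave at entry is a natural candidate for a strong prognostic factor. It should also bear on production-loss costs, since the Background attributes 93% of the national cost of low back pain to indirect costs.

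An unlisted covariate alone would not be a finding, because a list can be left to an analysis plan. The difficulty is the rule this protocol does fix: look at the baseline table, then decide. It has two weaknesses.

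1. *Necessary* is undefined, so the primary model depends on the data and on judgement.
2. The rule responds only to observed imbalance. Omitting a prognostic factor from a Cox model pulls the treatment hazard ratio toward 1 and costs power even when the arms are balanced.

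**Working it through.** **Inputs from the protocol (Sample size).** "We assume that a Hazard Ratio (HR) of 2.0 indicates a relevant difference"; "40 percent of the sick listed patients due to chronic low back pain does not return to work during the follow-up period"; "HR = 2, with a power (1-β) of 80% and a significance level of 5"%; 115 complete patients, 130 included, 10% dropout. Assumed because not stated: a two-sided test, 1:1 allocation, and the 40% applying to both arms together (60% events).

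**Step 1: the plan's own figure.** (1.96 + 0.8416)² = 7.849.
- Freedman: 7.849 × ((2+1)/(2−1))² = 70.6 events; 70.6/0.60 = 117.7 patients.
- Schoenfeld: 4 × 7.849/(ln 2)² = 65.3 events; 65.3/0.60 = 108.9 patients.
- The stated 115 lies between them, within 3% of Freedman. It gives 0.60 × 115 = 69 events, with power of 79.1% (Freedman) or 82.1% (Schoenfeld).
- Dropout: 115/0.9 = 127.8, so 128 against 130 stated.

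The sample size is reproduced, with little slack.

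**Step 2: power without and with the covariate.** Two separate simulations (A: 4,000 trials per scenario; B: 3,000) used 115 patients, exponential times, censoring at 12 months and 60% events overall. The treatment hazard ratio of 2.0 was taken as conditional on a binary partial/full covariate. The partial share and its RTW hazard ratio are assumptions.

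| RTW HR of partial | Partial share | A: power without / with | B: power without / with | B: mean unadjusted HR |
|---|---|---|---|---|
| 1.5 | 30% | 80.1 / 81.0 | 80.9 / 82.0 | 2.00 |
| 1.5 | 50% | 79.9 / 80.8 | 79.7 / 80.9 | 1.98 |
| 2 | 30% | 79.4 / 82.6 | 77.5 / 80.8 | 1.96 |
| 2 | 50% | 78.4 / 82.3 | 77.9 / 80.5 | 1.96 |
| 3 | 30% | 70.1 / 79.7 | 71.5 / 80.7 | 1.86 |
| 3 | 50% | 70.5 / 80.2 | 71.0 / 80.7 | 1.85 |

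The gains are 0.9 to 1.2, 2.6 to 3.9 and 9.2 to 9.7 points. With no prognostic effect (HR 1), B gave 81.7 without and 81.1 with, so an uninformative covariate costs under 1 point. The Monte Carlo standard error of one power figure in B is √(0.8 × 0.2/3,000) = 0.7 points.

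**Step 3: type I error.** With a treatment hazard ratio of 1 and a 50% partial share, B rejected in 5.5% (covariate HR 2) and 4.5% (HR 3) of trials unadjusted, and in 5.4% and 5.2% adjusted.

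**Step 4: chance imbalance.** The SD of the difference in partial share is √(2p(1−p)/m), with p independent of the strata.

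| m per arm | p | SD | P(difference of 10 points or more) |
|---|---|---|---|
| 65 (130/2) | 0.3 | 0.080 | 21% |
| 65 | 0.5 | 0.088 | 25% |
| 57.5 (115/2) | 0.3 | 0.085 | 24% |
| 57.5 | 0.5 | 0.093 | 28% |

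The approximate shift in the unadjusted hazard ratio is exp(0.10 × ln h): 1.04, 1.07 and 1.12 for h = 1.5, 2 and 3. Simulation B gave about 4%, 6 to 8% and 10 to 12%.

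**Step 5: costs.** If baseline sick leave explains a fraction R² of cost variance, the unadjusted standard error is 1/√(1−R²) times the adjusted one: 1.03, 1.05, 1.12 and 1.20 for R² = 5%, 10%, 20% and 30%. These R² values are assumptions.

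**The case against.** **The plan does allow adjustment.** A reader might infer that chance imbalance passes uncorrected into the hazard ratio. The protocol does not support that: a marked imbalance in partial sick leave could be adjusted for under the stated rule. What remains is that the rule is undefined and does nothing when the arms look alike. The Blinding section says data are analysed by code, which limits the room for favouring an arm but does not define the trigger.

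**Covariate lists belong in the analysis plan.** That is fair, and nothing here excludes baseline sick leave from the multivariate model. The point is therefore aimed at the trigger the protocol itself fixes.

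**A time-to-event outcome has no baseline value.** Correct in the sense used for the repeated measures: all patients are at risk at day 0, and the stated reason there is regression to the mean. Degree of sick leave is better called a likely prognostic factor, and the contrast with the secondary outcomes is only supporting evidence.

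**Baseline recording is not established.** Eligibility needs only some sick leave, and the percentage is described as a monthly item. The T0 tick makes recording likely, but it is an inference.

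**The power loss is hypothetical.** It depends on an undocumented prognostic strength and on reading the planned hazard ratio of 2.0 as conditional. If 2.0 is the marginal value, the unadjusted test keeps its planned power, and adjustment is a gain over the plan rather than repair of a shortfall. The shrinkage to about 1.86 partly reflects a different estimand.

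**The unadjusted cost comparison is valid.** A difference between randomized means is unbiased, and the 93% is a national cost share that does not show how much cost variance baseline sick leave explains. The cost point concerns precision only.

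**Conclusion.** The point holds as one of precision and pre-specification. Degree of sick leave at entry is neither balanced by design nor committed to the primary model, adjustment hangs on an undefined look at the data, and the cost difference has no stated adjustment.

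The size is conditional on the assumed prognostic hazard ratio: negligible at 1.5, modest at 2 and material at 3. The same holds for the shift caused by a chance imbalance.

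Two stronger readings fail. The documents do not show that the trial is underpowered, because they give neither the partial share nor its effect on RTW. Nor is there evidence of more false positives: the unadjusted and the fully adjusted tests both stay near 5%. The discretionary rule itself was not simulated, since it is not defined closely enough to simulate.

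The case for change rests on the low cost of committing in advance to a variable the trial probably collects.

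**What to change.** - **Data analysis.** For the primary Cox model, replace the conditional trigger with a fixed covariate set: sick-leave percentage at T0 (or partial versus full) and the two stratification factors, whatever the observed balance. Keep the unadjusted Kaplan-Meier, log-rank and hazard ratio results as supporting.
- **Economic evaluation.** Estimate the differences in indirect and total costs from a regression on treatment and baseline sick-leave percentage, with the same bias-corrected and accelerated bootstrap. Keep the raw mean differences as supporting.
- **Table 3.** Confirm that the T0 Return to work item records the percentage. If it does not, add it to the baseline questionnaire.

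The cost is a sentence or two in each section, no more patients, and no new data if T0 already holds the percentage. The Cox model would have four parameters on about 69 events (69/4 ≈ 17 per parameter), and its hazard ratio would be conditional on these covariates, which the report should say.

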##### MOC 3: The Graded Activity Program (GA)

This program is based on the principles of graded activity (GA) as developed by Lindström et al. [21,22] and on the operant (conditioning) model described by Fordyce [23]. It is adjusted to the Dutch situation in the study of Staal et al. 2004 [15]. The program used in this study has been adjusted to the particular study population of the BRIDGE-study. This GA program is provided by 10 regional physiotherapy practices located in Amsterdam or in the surrounding area. These practices have already been trained in the GA program in the context of other research projects [15,24,25]. Prior to the study, all physical therapist have followed a practical training course in the GA program (given by trainers) and were updated on the content of the BRIDGE-study.

The aim of the GA program is restoring occupational function and returning to previous work. Its aim is not pain reduction. The essence of the GA program is to implement an individually graded exercise program, which teaches the patient that it is safe to move while increasing the level of activity. During the GA program the patient has an active role in RTW and the physical therapist acts as a coach and supervisor, using a hands-off approach.

The GA program has two phases: 1. a baseline phase (pain/contingent); 2. a treatment phase (time/contingent). In Table 2 the content of the protocol is described. The entire program consists of maximally 26 sessions. The three baseline sessions have to be done in one week. The maximum duration is 12 weeks. However, the program stops as soon as a lasting return to own or equal work has been established. The session limit will not be communicated to the patient, because it will probably lead to a time lag regarding RTW.

**Table 2 T2:** Steps of the graded activity protocol

**Step**	**Characteristics**	
		The GA program starts within one week after the patient visits the care manager.

Before starting the baseline phase		-The PT performs a history-taking and a physical examination; -The PT gives counseling using the bio-psycho-social model on the development and maintenance and the consequences of pain; -The PT states that it is safe to start the GA program.

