**1 Baseline phase**	**Pain Contingent** Patient may stop at any time if he feels pain or other discomfort Individual training 3 sessions of 1.5 hour	- Baseline consists of 6 fixed and 3 free exercises (simulating work situation); - Aim is to determine the maximal performance for each exercise separately; - According to the results, a start quota (70% of the mean) and the load of each exercise session until the end of the program will be set; - The load of each quota depends on the date of full RTW; - When all quota are set, the PT will send the baseline results and the treatment report to the employee, the employer and the multidisciplinary team.

**2 Treatment phase**	**Time contingent** Pain is not a reason for stopping or altering the program Group training twice a week (4–6 persons) 1 hour per session	- The pre-set quota have to be followed strictly; - The PT accompanies the treatment sessions and evaluates the sessions; - A positive reinforcement will be given by the PT after completion of the quota; - When the date of RTW is within a few weeks, the learned behaviour and management of pain will be discussed. At this point the frequency of the sessions will be decreased to once a week until the patient returns to work; - When the employee fully returns to work or after 26 sessions the protocol will stop. A final communication form will be send to the multidisciplinary team.

		Every three weeks, the PT sends an evaluation form to the multidisciplinary team to report the progress of the treatment protocol.

		When the patient is sick listed because of LBP within 4 weeks after RTW, the GA program will be continued. It will again stop as soon as the patient fully returns to work, or all 26 sessions of the GA program are given.

GA, graded activity; PT, physical therapist; RTW, return to work; LBP, low back pain.

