##### 2. Usual clinical medical care (UC)

The patients who were allocated to the UC group receive the usual guidance by their medical specialist, occupational physician and general practitioner and allied health professionals. There are no specific requirements or restrictions with regard to type, duration or frequency of treatment. The patient's own general practitioner, occupational physician and treating medical specialist will be informed by letter about the study and the allocation of their patient to the UC group. They will be asked to adhere to their professional guidelines for LBP (if available) [1,3,4].

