### Co-interventions and compliance

During the intervention period co-interventions are discouraged, but cannot always be avoided. Asking patients and therapists independently about all interventions applied will assess the compliance to the multidisciplinary outpatient care program. Information about all treatments and co-interventions received by the patients in the multidisciplinary outpatient care and UC group, are collected by means of cost-diaries and questionnaires.

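### The per-protocol comparison in effect drops patients from one arm only, so it cannot show whether the intention-to-treat result is biased

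*Protocol article*

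**What the plan says.** Under Data analysis, the protocol article makes ITT the governing principle: "All statistical analyses will be performed according to the intention-to-treat principle". It then adds a second analysis and gives its purpose: "In order to assess whether protocol deviations have caused bias, the results of the intention-to-treat analyses will be compared to per-protocol analyses". The per-protocol set is defined in one sentence: "Only those patients who complied fully with the intervention protocol will be included". That section states no separate criterion for UC patients.

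Four other places bear on who can be excluded:

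- Usual clinical medical care (UC): "There are no specific requirements or restrictions with regard to type, duration or frequency of treatment".
- Co-interventions and compliance: asking patients and therapists about the interventions applied "will assess the compliance to the multidisciplinary outpatient care program". No parallel compliance measure is described for UC.
- The same section: "During the intervention period co-interventions are discouraged, but cannot always be avoided". Co-interventions are recorded in both groups but are not named as a per-protocol criterion.
- MOC 3, on graded activity: "the program stops as soon as a lasting return to own or equal work has been established". Table 2 adds: "When the employee fully returns to work or after 26 sessions the protocol will stop".

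**The concern.** There are two linked problems.

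The first is the purpose given to the comparison. ITT compares the groups as randomized. Deviations change what was delivered, and so can shrink the effect of being assigned to MOC, but they do not make the randomized groups unlike each other. The per-protocol set is chosen after randomization and is the contrast open to selection. Using it as the yardstick for bias in ITT reverses the logic.

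The second is that the selection acts on one arm. If only MOC patients can fail the criterion, MOC loses its non-compliers while UC keeps the patients who would have been non-compliers had they been assigned to MOC. Compliance may also be tied to the outcome, because graded activity ends at lasting RTW: the time available in which to deviate depends on how soon the patient returns.

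At stake is how a discrepancy would be read. A modest ITT HR beside a larger per-protocol HR could be taken as a real effect diluted by deviations, when selection alone could produce the gap.

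**Working it through.** **Inputs from the protocol article.** Sample size section: 115 complete patients, 130 included, HR 2.0, 80% power, 5% significance, 40% not returning within 12 months (60% events), 10% dropout. Randomization section: blocks of 4 to avoid unequal groups, read here as 1:1, or 58 per arm. MOC 3: graded activity lasts at most 12 weeks.

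**Assumptions, because the article gives no figures.** Compliance proportion c of 50%, 70% or 90%; compliers' RTW hazard k times that of non-compliers; constant hazards; two-sided 5% test.

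**1. The plan's own figure.** Freedman's formula gives events = (1.960 + 0.842)² × ((2 + 1)/(2 − 1))² = 7.849 × 9 = 70.64. Then 70.64/0.60 = 117.7, so 118 patients (stated 115), and 118/0.9 = 131.1, so 132 (stated 130). Both are within 3%, so the 60% event proportion is a fair basis for what follows. The point does not depend on the sample size.

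**2. What one-arm exclusion does when the program has no effect.** Let x be the proportion of non-compliers still off work at 12 months. Compliers then have x^k, and the whole group must satisfy c·x^k + (1 − c)·x = 0.40.

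For c = 0.7 and k = 2: 0.7x² + 0.3x = 0.4, so x = (−0.3 + √1.21)/1.4 = 0.571 and x² = 0.327. RTW is 67.3% in compliers and 42.9% in non-compliers; 0.7 × 67.3 + 0.3 × 42.9 = 60.0%, as required. The per-protocol analysis would set 67.3% (MOC compliers) against 60% (all UC) although the program did nothing. The ratio of cumulative hazards is ln(0.327)/ln(0.40) = 1.22, close to the Cox value below.

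**3. Simulation.** True HR 1, non-compliers removed from MOC only, log-rank test in 4,000 trials per scenario; expected HR from a large-sample Cox model.

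| Compliers' hazard vs non-compliers' | Per-protocol HR at 50 / 70 / 90% compliance | False significant benefit (nominal 2.5%) |
|---|---|---|
| 3 times | 1.68 / 1.33 / 1.10 | 49 / 20 / 6% |
| 2 times | 1.40 / 1.20 / 1.06 | 24 / 11 / 5% |
| equal | 1.00 / 1.01 / 1.00 | 3 / 3 / 3% |
| 0.5 times | 0.70 / 0.81 / 0.93 | 0.1 / 0.3 / 1.2% |

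The ITT test rejected in 4.9–5.6% of trials throughout (nominal 5%).

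**4. The link with the stopping of graded activity.** Here compliance is unrelated to prognosis, and only its definition matters.

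- Deviation accrues over 12 weeks and RTW ends the risk. With a 12-week deviation risk of 10 / 30 / 50%, the HR is 1.02 / 1.06 / 1.14 and false benefit occurs in 3 / 5 / 7% of trials.
- Full compliance means staying in the program for all 12 weeks, so early returners are removed. The HR is about 0.70 at each risk, and false significant harm occurs in 26 / 21 / 16% of trials. As a check, patients kept in MOC have only 40 of 52 weeks in which to return, so 0.40^(40/52) = 0.494 remain off work: 50.6% RTW against 60% in UC.

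**The case against.** **The one-arm exclusion is not written down.** This is true: it is an inference. Usual care is listed under Interventions, its clinicians are asked to follow their guidelines, and co-interventions are recorded in both groups, so a UC deviation could in principle be defined. A condensed article may also leave the rule for each arm to a fuller document. The inference still follows from the text shown, since the criterion is compliance with the intervention protocol, compliance is assessed for MOC, and UC has no treatment requirements. The stated purpose of the comparison would remain wrong even with a rule for both arms, because the set would still be selected after randomization.

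**A reader might infer that the analysis is bound to show a spurious benefit.** The documents do not support that. They do not establish that compliers have the better prognosis. Benefit is the more plausible direction, because stopping at full RTW is itself what the protocol prescribes, and because the workplace intervention relies on commitment from patient and employer, which may itself favour RTW. But the bias vanishes if compliance is unrelated to prognosis and reverses under another reading of full compliance.

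**A reader might also infer that the trial's main conclusion is compromised.** It is not. ITT governs the analyses, and no decision rule is attached to the per-protocol result. The sentence may be no more than a loosely worded sensitivity check. This limits the seriousness but does not make the stated inference valid.

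**Conclusion.** The point holds as a flaw in a secondary analysis that should be corrected. The per-protocol set is selected after randomization and, as written, in effect from the MOC arm alone, so its difference from ITT cannot show that ITT is biased.

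Under no effect, the scenarios examined give per-protocol HRs from about 0.70 to 1.68. With a two-fold hazard ratio between compliers and non-compliers, the range is 1.06–1.40. These sizes rest on assumed compliance, assumed prognostic contrast, constant hazards and 58 patients per arm, and are illustrations, not predictions. The logical point needs none of them.

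ITT is not immune to every bias: the expected 10% dropout and unblinded self-report are separate issues. A per-protocol comparison would not diagnose those either.

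**What to change.** 1. Delete the statement that comparing per-protocol with ITT results assesses bias from protocol deviations.
2. Define compliance in advance by starting the components (care-manager visit, first workplace visit, first graded activity session), not by sessions completed. This largely frees it from RTW, though a very early returner could still miss a first visit. State what, if anything, counts as a deviation in UC.
3. As the secondary analysis of the effect of receiving the program, report a complier-average effect with randomization as instrument. For RTW by 12 months: (RTW proportion in MOC − RTW proportion in UC) / (proportion starting the program in MOC − proportion receiving the equivalent in UC). With no effect the numerator is centred on zero, whatever the prognosis of compliers.
4. State its assumptions. UC patients may receive similar components: UC treatment is unrestricted, patients have direct access to allied health professionals, and the physiotherapy practices were already trained in graded activity through other projects. The denominator therefore cannot simply be taken as the MOC starting proportion. Partial receipt of a three-part program and extra attention in an unblinded trial also strain the assumption that assignment acts only through starting it.
5. Label any naive per-protocol result as descriptive only.

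The cost is some extra analysis. Compliance and co-intervention data are already to be collected. The confidence interval will be wider: at 70% starting in MOC and none in UC, roughly 1/0.7 = 1.4 times that of the ITT risk difference.
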